### Data collection

Patients were first involved in this research at a patient event hosted by Xi’an AIER Eye Hospital. Topics on which opinions were collected included randomization, cross-over, and the duration of follow-up of trial patients. The staff members from Xi’an AIER Eye Hospital refractive center were responsible for generating the allocation sequence and enrolling participants. The trained research nurses, supervised by the surgeon, will obtain written consent from participants in the trial. The investigators will communicate a summary of the trial results to participants. The burden of the intervention was discussed at our initial meeting with patients and at the consent-taking stage in the trial. All patients will have data collection forms outlining the schedule of each follow-up visit and data to be collected at each visit, which include visual acuity, refraction results, clinical examination, and other outcome measures as described above. According to our previous experience and strategies for adherence, few patients will discontinue or deviate from the protocol. However, participants may withdraw from the study for any reason at any time. The primary and secondary outcomes will be collected from patients discontinued from the study at the last follow-up visit. Furthermore, the effect that any missing data might have on results will be assessed via sensitivity analysis. Dropouts (participants who non-adherence or discontinue from the protocol) will be included in the analysis by modern imputation methods for missing data. All data access and trial conduct will be monitored by the supervisors ([name] and [name]). An interim analysis will be performed on the primary endpoint when 50% of patients have been randomized and have completed the 3 months follow-up. The interim analysis will be performed by an independent statistician who is blinded for the treatment allocation. The statistician will report to the AIER central ethics committee (ACEC). The ACEC will have access to all data and will discuss the results of the interim analysis. The ACEC will decide on the continuation or stopping of the trial according to interim-analysis results. At the end of the study, the research data will be entered by the research assistant and stored for up to 3 years in compliance with any integrity issues that may arise from any subsequent publications. Following that time period, the data will be kept under the control of the supervisor. The technical appendix, statistical code, and dataset are available from the Dryad repository, https://doi.org/10.5061/dryad.0vt4b8h1g.

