### Sample size

As this is a non-inferiority trial with a binary outcome, we have calculated the required sample size using the maximum likelihood method for a large sample [20]. A review of the current literature reveals that the reported refractive predictabilities in ICL and SMILE range from 90.0% [12] to 97% [15] and from 93% [4] to 99% [5], respectively. We therefore assumed the refractive predictabilities in ICL and SMILE in this study are 95% and 97%, respectively. Thus, a sample size of 200 subjects (400 eyes) was deemed to be sufficient to confirm non-inferiority with a power of ≥ 80% and at a 5% significance level using a 2% non-inferiority margin, which is the clinically significant difference from our preliminary data. To account for a lost to follow-up rate of 30%, 300 subjects will be recruited instead of 200. Patients will be recruited for this trial through two primary mechanisms: local advertising and research patient database. Local advertising takes advantage of the audio-visual media as well as internet social platform. The Xi’an AIER refractive error patient registry (database) has been maintained since 2017 and currently contains more than ten thousand patients (more than 12 million people now live in the city).

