### Statistical analyses

Demographic and baseline information will be described, and eye-specific characteristics will be described for either arm. To study the non-inferiority of ICL to SMILE, a 90% confidence interval (CI) of the difference in predictability between the two treatments (SMILE minus ICL) using a linear mixed model. If the upper limit of the 90% CI does not exceed the pre-defined non-inferiority margin of 2%, non-inferiority is confirmed. Similarly, for each of the two secondary outcomes, efficacy, and safety, a 90% CI of the difference between the two treatments using the above-mentioned method will be constructed and then compared with a non-inferiority margin of 2%. Assuming the other secondary outcome, HOA, follows a normal distribution, a 90% CI of the difference between the two treatments will be constructed through the linear mixed model, and then compared with a non-inferiority margin of 2%. All the statistical analyses of the data will be performed using SPSS 23.0 (Inc, Chicago, IL) package. Normality of data will be examined by histogram frequency analysis and the Shapiro–Wilk test. Data will be presented as the mean ± standard deviation (SD) for continuous variables. Student’s *t*-test and ANOVA for normally distributed variables or Mann–Whitney *U* test for skewed distributions will be used to compare differences, while the proportion for categorical data and chi-squared or Fisher’s exact test to test statistical significance. All statistical tests used a 2-sided *P* value of 0.05.

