## Trial status

Ongoing. This protocol is the second version and is revised on Jan 2022. Recruitment commenced on May 2018, and follow-up of the last recruited patient is estimated to complete on Dec 2022.

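### The interim analysis can stop the trial on the primary endpoint with no stated direction or boundary, while the final non-inferiority test keeps an unadjusted 90% CI

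*Protocol article*

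**What the plan says.** Four statements in the protocol article bear on this point.

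- **Timing and endpoint (Data collection):** "An interim analysis will be performed on the primary endpoint when 50% of patients have been randomized and have completed the 3 months follow-up".
- **Who does it and who decides (Data collection):** "The interim analysis will be performed by an independent statistician who is blinded for the treatment allocation". The statistician reports to the AIER central ethics committee (ACEC), which may see all data. Then: "The ACEC will decide on the continuation or stopping of the trial according to interim-analysis results".
- **Final rule (Statistical analyses):** for the difference SMILE minus ICL, "If the upper limit of the 90% CI does not exceed the pre-defined non-inferiority margin of 2%, non-inferiority is confirmed". This section does not mention the interim. The Sample size section likewise works "at a 5% significance level using a 2% non-inferiority margin", with no allowance for an earlier look.
- **Data entry (Data collection):** "At the end of the study, the research data will be entered by the research assistant".

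**The concern.** A committee may end the trial on results for the confirmatory endpoint, and the text does not limit what kind of result justifies that. The only criterion given anywhere for this endpoint is the 90% CI against 2%, and it is kept at full strength for the final analysis. A reader who follows the text as written could stop at half the trial because the 90% CI lies below 2%, declare non-inferiority, and otherwise test again at the same level at the end. That gives the false claim two chances at 5% each. The trial's single confirmatory conclusion would then carry a higher error rate than the one stated.

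A smaller conflict sits in the same section. An analysis at the halfway point needs data that have been entered by then, but the text places data entry at the end of the study.

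**Working it through.** **Inputs**

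- Interim at 50% of patients with 3-month data (Data collection): 150 of 300. I take the information fraction as t = 0.5; this is an assumption, so a range is shown.
- Final rule: upper limit of a two-sided 90% CI not above 2% (Statistical analyses).
- Significance level 5% (Sample size).
- Assumed for the calculation: one threshold at one visit, tested at both looks. The Outcomes section defines the primary outcome by two thresholds at every visit, so the document does not fix which one the interim tests.

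**Step 1. The plan's own level, one look.** A two-sided 90% CI leaves 5% in each tail, so the critical value is z = 1.645 and the false non-inferiority rate is 5%. This agrees with the Sample size section.

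**Step 2. Two looks on the same rule.** At the margin, Z1 (interim) and Z2 (final) are standard normal with correlation √t = √0.5 = 0.707.

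P(Z1 > 1.645 or Z2 > 1.645) = 0.05 + 0.05 − P(both > 1.645) = 0.100 − 0.0199 = 0.080.

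| Information fraction | Overall one-sided error |
|---|---|
| 0.4 | 0.083 |
| 0.5 | 0.080 |
| 0.6 | 0.077 |
| 0.75 | 0.071 |

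**Step 3. Other readings of the interim, t = 0.5.**

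- *Futility only*, for example stopping if Z1 < 0: P(Z1 > 0 and Z2 > 1.645) = 0.049. The 5% is not exceeded.
- *Harm only, or a pooled look without comparison by arm*: no non-inferiority claim is possible at the interim, so nothing is added to the 5%.
- *Haybittle-Peto bound, z > 3, final z still 1.645*: 0.00135 + 0.05 − P(Z1 > 3 and Z2 > 1.645) = 0.05135 − 0.00111 = 0.0502.

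**Step 4. Boundaries that hold 5% exactly, t = 0.5.**

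| Boundary | Interim one-sided level | Final one-sided level | Final CI |
|---|---|---|---|
| Lan-DeMets O'Brien-Fleming | 0.0056 | 0.0482 | about 90.4% |
| O'Brien-Fleming | 0.0088 | 0.0467 | about 90.7% |
| Pocock | 0.0304 | 0.0304 | about 93.9% |

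The final CI level is 1 − 2 × the final one-sided level; for O'Brien-Fleming, 1 − 2 × 0.0467 = 0.907.

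**Step 5. Dates.** Follow-up lasts 18 months, and "follow-up of the last recruited patient is estimated to complete on Dec 2022". December 2022 less 18 months is June 2021 for the last randomization. Recruitment began in May 2018, so accrual ran about 37 months. If accrual was even (an assumption), half were in at 18.5 months and had 3-month data at 21.5 months, around February to March 2020. At that point 21.5/37 = 58% had been recruited and about 42% had not.

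**The case against.** The strongest reply is that this is a condensed article, and that stopping boundaries usually stand in the full protocol or analysis plan, which are not shown. That is fair for the boundary itself. The unadjusted 90% CI does not prove an error either: Step 3 shows that it is compatible with a futility-only look, a harm-only look or a very strict bound. What remains is that the article does fix some things. It gives the committee an unrestricted power to stop on the primary endpoint, and it fixes the final test at full level. Any of the three boundaries in Step 4 would need a final CI wider than the 90% stated. The two statements need a sentence that joins them.

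The 8.0% is also conditional. The document nowhere says that the 90% CI rule applies at the interim, so the figure is what the wording permits and not what the plan prescribes.

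Three stronger readings are tempting, and the documents do not support them.

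- *That the interim comes too late to be of use.* A reader may infer this because recruitment must have ended by about June 2021 and the January 2022 version still puts the interim in the future tense. But even accrual places the trigger in early 2020, when some 42% were still to be recruited. The tense shows little, since the Sample size section also uses the future for recruitment that was over on the stated dates. The document does not say whether the look was held.
- *That a masked statistician cannot apply a directional rule.* Coded arms can be compared, and the deciding committee has access to all data, so direction can be resolved there.
- *That the interim must be deleted.* That is a preference. Stating what it may be used for is enough.

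The data-entry sentence may be loose wording, since the same section provides forms for each visit. It still contradicts an interim analysis as it stands.

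**Conclusion.** The point holds as a conditional one. As written, the article permits a stop for non-inferiority at half the trial with no control of the error rate. If that option were used on the 90% CI rule, overall one-sided error would be about 8.0% instead of 5%, and between 8.3% and 7.7% for information fractions of 0.4 to 0.6. This rests on a comparative look, on stopping to declare non-inferiority, and on the same endpoint at both looks. Without the first two there is no inflation. The conflict between end-of-study data entry and a halfway analysis is real but minor. Whether the interim took place is open and should be stated before the final analysis, because the meaning of the final 90% CI depends on it.

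**What to change.** In Data collection and in Statistical analyses, adopt one of these:

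1. State that no non-inferiority claim can be made at the interim, say what the committee may stop for, and keep the final 90% CI.
2. Allow a non-inferiority stop only on a Haybittle-Peto bound (z > 3, about a 99.7% CI). The final 90% CI can stay essentially unchanged, with overall error about 5.02%.
3. Name another boundary and replace the final 90% CI by the matching wider one, as in Step 4.

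Then state whether and when the interim took place. If it did, report its result and the criterion actually used; a rule that was not in force at the time should not be written in afterwards as if it had been. Finally, reword the data-entry sentence so that it fits an analysis at 50% of patients.

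The cost is a few sentences. The sponsor gives up early stopping for non-inferiority under option 1 and makes it harder under option 2. Under option 3 it accepts a slightly to moderately wider final interval, from about 90.4% to 93.9% depending on the boundary.

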
### Adverse events

Patients are assessed for adverse events during surgery and at all postoperative visits following randomization.Frequency of intraoperative events: for ICL/TICL, adverse events include lens impairment, ICL flip, iris prolapse, and hyphema; for SMILE, adverse events include suction loss, opaque bubble layer (OBL), black spots, lenticule remnants, and decentration.Frequency of postoperative events: for ICL, we document the frequency of adverse events such as ocular hypertension, transient corneal edema, corneal endodermis damage, vault abnormality, surgery-related cataract, and intraocular infection; for SMILE, we document the frequency of adverse events such as infectious keratitis, diffuse lamellar keratitis (DLK), transient light sensitivity syndrome (TLSS), surgery related-cornea ectasia, and refractive regression.

All adverse events will be reported to both the centralized institution review board and institution heads (AIER Eye Group). The AIER Eye Group has insurance to cover for non-negligent harm associated with the trial. This will include coverage for additional health care or compensation according to study insurance policies.

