**Methods/design:**

This is a prospective randomized study. A total of 300 participants will be randomized into two groups, the ICL/TICL group and SMILE group. Eligible participants with spherical equivalent (SE) less than − 6.0 diopter (D) will be recruited. Following randomization, participants will be followed at 1, 3, 6, 12, and 18 months. The primary outcome is the refractive predictability at every postoperative point after surgery, which is the proportion of the number of eyes achieving a postoperative SE within ± 0.5 D and ± 1.0 D of the intended target. Secondary outcome parameters include visual acuity, refraction, adverse events, and quality of vision measurements.

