#### SMILE procedure

In the SMILE group, the VisuMax 500-kHz femtosecond laser (Visumax, Carl Zeiss Meditec AG) is used to create the femtosecond laser dissection planes for SMILE. The spot distance is 3 mm for lamellar cuts and 2 mm for side cuts. The spot energy is set to 140 to 150 nJ. The minimum lenticule side-cut thickness is set to 10 mm. The cap diameter is 7.5 mm with a 2.5-mm side-cut and a side-cut angle of 90°. After surgery, patients receive levofloxacin 0.5% eyedrops (Cravit; Santen, Osaka, Japan) and dexamethasone 0.1% eyedrops (Maxidex; Alcon-Couvreur, Puurs, Belgium) 4 times daily for 2 weeks. Artificial tears (HYCOSAN 0.1%; URSAPHARM Arzneimittel GmbH, Saarbrücken, Germany) are prescribed after surgery, and the dosage is adjusted based on the patients’ symptoms.

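### Events that either procedure can produce are named for documentation in one arm only, which puts any between-arm comparison of adverse-event frequency at risk of ascertainment bias

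*Protocol article*

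**What the plan says.** The Adverse events section starts with a general rule for everyone: "Patients are assessed for adverse events during surgery and at all postoperative visits following randomization". It then splits by arm. After ICL, "for ICL, we document the frequency of adverse events such as ocular hypertension, transient corneal edema, corneal endodermis damage, vault abnormality", followed by cataract and intraocular infection. After SMILE, "for SMILE, we document the frequency of adverse events such as infectious keratitis, diffuse lamellar keratitis (DLK), transient light sensitivity syndrome (TLSS", followed by "surgery related-cornea ectasia, and refractive regression". Both lists are introduced as examples. The section closes by stating that all adverse events go to the review board and the institution heads.

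Four other places bear on this:
- The Abstract makes adverse events an outcome: "Secondary outcome parameters include visual acuity, refraction, adverse events, and quality of vision measurements".
- The Discussion says the non-inferiority design is used to compare the primary and secondary outcomes.
- Statistical analyses plans, "for each of the two secondary outcomes, efficacy, and safety, a 90% CI of the difference between the two treatments", a comparison with a 2% margin. It does not say which variable represents safety.
- Study design and randomization says that surgeons and participants cannot be masked and that masked optometrists take the follow-up measurements.

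**The concern.** Separate lists are right for events that only one procedure can cause, such as ICL flip, vault abnormality, suction loss or lenticule remnants. They are a weakness for events that either arm can show. A prompt that names an event in one arm invites staff to look for it and record it there, and to do so less consistently in the other arm. Staff who know the allocation are the ones most easily steered by such prompts.

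At stake is whether a difference in adverse-event frequency can be read as a difference between the procedures. The bias has no fixed direction. Prompting for ocular hypertension only after ICL would count against ICL, and prompting for regression only after SMILE would count in its favour.

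**Working it through.** **1. Can the events named in one arm arise in both?**

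| Event | Named for | Evidence that it is possible or measured in both arms |
|---|---|---|
| Refractive regression | SMILE only | Study design and randomization bars retreatment for regression for all participants. Outcomes and trial duration lists refraction without arm restriction, and missing the refractive target is what the primary outcome counts in both arms. |
| Ocular hypertension | ICL only | Outcomes and trial duration lists change in intraocular pressure without arm restriction, in a section that opens with all patients being assessed. |
| Transient corneal edema | ICL only | No shared measurement is named, so this event depends most on prompting. |
| Infection | Both, under different terms | Intraocular infection for ICL, infectious keratitis for SMILE. |

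One caution on pressure: the same outcome item includes lens vault, which the adverse-event lists treat as an ICL matter. It should therefore be confirmed that pressure is measured in both arms. Baseline assessment does not list a pressure reading, although an outcome defined as change implies one.

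**2. How large could the distortion be?** The documents give no adverse-event rate, so there is no figure of theirs to reproduce. Let r be the true rate, equal in both arms, and let a and b be the shares of true events recorded under ICL and SMILE. The expected artificial difference (ICL minus SMILE) is r × (a − b). Equal recording gives 0. Recording under ICL only (a = 1, b = 0) gives r. Half recording under SMILE at r = 3% gives 0.03 × (1 − 0.5) = 1.5 points. None of r, a and b is in the documents.

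**3. Illustration against the 2% margin.** Assumptions: 200 eyes per arm (the 400 eyes of the Sample size section, split equally), eyes treated as independent, r assumed, and recording either complete or absent. Expected upper 90% limits for ICL minus SMILE:
- Recorded under ICL only: r + 1.645 × √(r(1−r)/200)
- Common list: 0 + 1.645 × √(2r(1−r)/200)
- Recorded under SMILE only: −r + 1.645 × √(r(1−r)/200)

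| Assumed r | ICL only | Common list | SMILE only |
|---|---|---|---|
| 1% | 2.2% | 1.6% | 0.2% |
| 2% | 3.6% | 2.3% | −0.4% |
| 3% | 5.0% | 2.8% | −1.0% |
| 5% | 7.5% | 3.6% | −2.5% |
| 10% | 13.5% | 4.9% | −6.5% |

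At r = 1%, recording under ICL only moves the expected limit from below 2% to above it. From r = 2% upwards the common list already exceeds 2%, so recording under ICL only changes the estimate but not the expected result. Recording under SMILE only would bring the limit below 2% at every rate shown. These figures show the mechanism at its extreme. They do not predict what this trial will find.

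**The case against.** The strongest reply is that the text contains no rule limiting what is counted. The lists are examples, every patient is assessed at every visit, and all adverse events are reported whatever the arm. Pressure and refraction are outcomes in their own right, and masked optometrists take the follow-up measurements. Event definitions and form content are commonly left to the full protocol, and the definition of safety to the analysis plan.

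Much of this stands, and it rules out several stronger readings that a reader might infer:
- *Ocular hypertension is counted only after ICL and regression only after SMILE.* Illustrative lists and the rule that all events are reported do not support this.
- *The planned safety comparison is built from these lists.* Statistical analyses does not link the two, and the outcomes section holds other safety-related measures (CDVA, intraocular pressure, endothelial cell count).
- *The SMILE arm's steroid drops make the omission of ocular hypertension there worse.* The protocol draws no link between the drops and pressure.
- *Dry eye is a laser harm left off both lists.* The Background cites less iatrogenic dry eye as an advantage of SMILE, and an illustrative list need not name every event.

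The reply does not remove the asymmetry that the article itself states. Reporting every event to a board does not secure equal definitions or equal searching, and a comparison of frequencies needs both. Masked measurement protects a measured quantity. The article does not say that it also governs which adverse events are recorded.

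**Conclusion.** The point holds as a risk, not as a demonstrated bias. The protocol names ocular hypertension and transient corneal edema for documentation only under ICL, and refractive regression only under SMILE, although its own text treats regression as possible in all participants and sets no arm limit on pressure or refraction. With unmasked surgeons, any between-arm comparison of adverse-event frequency is open to ascertainment bias in either direction.

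The size cannot be derived from the documents. The illustration rests on assumed rates, all-or-nothing recording and independent eyes. It would bear on the 2% safety comparison only if safety were built from these events, which the protocol does not state. The primary outcome is not affected. The weakness is worth correcting because most of it can be removed with data already planned.

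**What to change.** In Adverse events, set one common list of events possible in both arms: at least ocular hypertension, corneal edema, infection, cataract, refractive regression and loss of CDVA lines. Use identical definitions and ascertainment in both arms. Derive ocular hypertension, regression and CDVA loss from the pressure, refraction and CDVA data planned for all patients, and state plainly that pressure is measured in both arms. Leave dry eye off this list, since no dry-eye assessment is planned.

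Restrict between-arm comparisons of adverse events to the common list. Report procedure-specific events (ICL flip, vault abnormality, suction loss, opaque bubble layer, diffuse lamellar keratitis) descriptively by arm.

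In Statistical analyses, tie safety to one binary variable that both arms already supply, such as the proportion of eyes losing CDVA lines, and state the sign. The primary comparison is SMILE minus ICL with an upper limit of 2%, which suits a favourable outcome. Carried over unchanged to a harm, it would turn an ICL excess into a negative difference that passes. For a harm, the difference must be signed so that an ICL excess counts against ICL.

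The cost is minor form and derivation work. Recruitment began in May 2018 and follow-up was expected to end in December 2022, so events that cannot be derived from recorded measurements, such as transient corneal edema, cannot be recovered for past visits. That limitation should be reported.
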